## Abstract

Vaccines against COVID-19 approved for use in the EU/EEA have been shown to be highly effective against wild-type SARS-CoV-2. However, their effectiveness against new variants may be reduced. This study aims to evaluate the effectiveness of vaccines against COVID-19 in the prevention of symptomatic and severe disease, during pre- and post-omicron phases. Individuals who sought treatment at the emergency department of a Portuguese hospital with COVID-19-like disease and were tested for SARS-CoV-2 are the subjects of the study. Patients who received a positive result are considered cases, while those with negative results are the controls. The test-negative case–control method is one of the study designs recommended by WHO to estimate the effectiveness of vaccines against COVID-19. The main advantage of this design is that it controls for the healthcare seeking bias, commonly present in traditional cohort and case–control designs. This study may have broad implications for understanding the real-world performance of the COVID-19 vaccines at the local level, which may play a key role in promoting adherence to vaccination. Moreover, this study may contribute to inform decisions regarding booster doses and variant-specific vaccine formulations leading to the control of this and future pandemics.

## 1. Introduction

Vaccines against COVID-19 were launched as a promising tool in prevention and control of the current pandemic. As of 1 April 2022, there were 349 vaccines under development worldwide, of which 153 are in clinical trials [1]. The European Commission has already granted conditional marketing authorization for five vaccines, including RNA vaccines (i.e., Comirnaty and Spikevax), adenovirus vector vaccines (i.e., Vaxzevria and COVID-19 vaccine Janssen) and a recombinant protein vaccine (i.e., Nuvaxovid).

Vaccine performance can be assessed by efficacy, effectiveness and impact. A vaccine’s efficacy is its ability to reduce the infection or disease risk among the vaccinated in controlled and ideal conditions, usually estimated in randomized controlled trials [2]. Effectiveness is the reduction in infection or disease risk among vaccinated through vaccination in real-world conditions assessed in observational studies [2]. A vaccine’s impact comprises the reduction in the incidence of infection or disease in a population in which some of its members are vaccinated. The impact of a vaccine depends on the vaccination coverage and results: on the one hand of direct effects of vaccination in vaccinated people and, on the other hand, of any indirect effect on vaccinated and non-vaccinated people through herd immunity [3,4]. The impact may also relate to other variables beyond the disease, such as health systems’ functioning and socioeconomic indicators.

According to the World Health Organization (WHO) guidelines, the primary efficacy point estimate should be at least 50% so that a vaccine is approved [5]. COVID-19 vaccines already authorized for use in European Union and European Economic Area achieved the efficacy of up to 96.4% in initial clinical trials [6,7,8,9,10]. After being considered efficacious in trials, experimental studies raise ethical concerns, as they need a control group that would be deprived from the benefits of vaccination [11]. Therefore, and according to the WHO’s recommendations, the performance of vaccines must also be evaluated under real-world conditions and using data from observational studies [2].

Two systematic reviews with meta-analysis showed that the vaccine effectiveness against the SARS-CoV-2 infection ranged from 70 to 90% for the wild-type strains [12,13]. However, concerns have been raised regarding reduced vaccine effectiveness against new variants of concern (VoC) [14].

As of 10 March 2022, Portugal had over three million cumulative laboratory-confirmed cases of SARS-CoV-2, emerging from five waves of infection, as can be seen in Figure 1 [15]. Delta variant (B.1.617.2) appeared in India in December 2020 and rapidly spread worldwide, becoming dominant by August 2021 in Portugal. It has been shown to be more transmissible and virulent than the Alpha variant [16]. Additionally, a study performed in Portugal showed significantly higher odds of vaccine breakthrough infection in Delta-infected patients than in Alpha-infected, suggesting lower effectiveness of the mRNA vaccines in preventing infection with the Delta variant [17], which is consistent with other studies [18,19].

The B.1.1.529 (Omicron) variant was first found in South Africa in November 2021, and it quickly spread worldwide. Omicron variant was shown to be 2.8-times more infectious than the Delta [20] and was responsible for the fifth pandemic wave in Portugal, which reached its peak on the 25 January 2022 with 5598 cases per million inhabitants. Omicron has shown immunity escaping capacity in laboratory studies and booster vaccine doses may be essential to overcome this [21,22].

This article presents the study protocol for evaluating the effectiveness of vaccines against COVID-19 in the prevention of symptomatic and severe disease in a district located in the northern region of Portugal, using a retrospective test-negative case–control design.

We will perform a comparative analysis between the fourth pandemic wave (1 June to 30 September 2021), dominated by Alpha and Delta variants and the fifth pandemic wave (1 November 2021 to 2 March 2022), Omicron-dominant, represented in Figure 1. In the beginning of the first period, the Alpha variant was dominant in Portugal, and by the week of 21 to 27 June 2021, the Delta variant became dominant [23]. The fifth wave of infection in Portugal, corresponding to our second period in analysis, was dominated by the Omicron variant since the week of 20 to 26 December 2021 [24].

The vaccination campaign in Portugal started on 27 December 2020. At that time, it only began with Comirnaty from Pfizer-BioNTech. In the first weeks of January, the first batch of Spikevax (previously COVID-19 vaccine Moderna) arrived in Portugal and soon began to be administrated. On the 7 February 2021, the first batch of Vaxzevria (previously COVID-19 Vaccine AstraZeneca) arrived, and on the 14 April 2021, the first batch of Jcovden (previously COVID-19 vaccine Janssen) was delivered in Portugal. Therefore, the four vaccines used in Portugal at that time were already in circulation in both periods of the study.

Monitoring mass-vaccination campaigns is essential for the prevention and control of emerging diseases. As new variants of concern emerge, early evidence on the effectiveness of vaccines is essential for informing policy decisions. Are booster doses effective? How long does their effect last? How should we prioritize booster doses over other non-pharmacological measures? Moreover, vaccine performances may be different when they are used in specific populations, different geographic settings and throughout different pandemic phases [2]. Thus, vaccines’ effectiveness should be assessed either at the local, regional, national and international levels.

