## 2. Materials and Methods

We will perform an observational study using a retrospective test-negative case–control design. This method has been used successfully to estimate the effectiveness of vaccines against respiratory diseases such as influenza virus infection [25,26,27] and COVID-19 [28,29,30,31,32].

A test-negative study is considered a variant of the traditional case–control design: the study population is composed by individuals who have a predefined set of symptoms, seek help at the same healthcare unit and are tested by the same methodology, in this case, real-time reverse transcription polymerase chain reaction (rRT-PCR) or an antigen test for SARS-CoV-2. The cases are individuals who receive a positive result and controls are those with a negative result [2,33].

Patients with COVID-19-like illness admitted to the Hospital of Viana do Castelo and Hospital of Ponte de Lima from 1 June 2021 until 2 March 2022, will be enrolled. These hospitals serve a population of 231,293 people resident in the district of Viana do Castelo, located in the northern region of Portugal, as shown in Figure 2.

Patients will be eligible if they are aged 18 years old or above on the date of hospital admission, resident in the district of Viana do Castelo, meeting any of the WHO clinical criteria for COVID-19, namely acute onset of fever, cough, general weakness, fatigue, headache, myalgias, sore throat, coryza, dyspnoea, recent onset of anosmia or dysgeusia, anorexia, nausea, vomiting, diarrhoea or altered mental status who received rRT-PCR or antigen testing for SARS-CoV-2 within 10 days of illness onset.

Exclusion criteria include patients not eligible for vaccination against COVID-19 or without information on the vaccination status and without SARS-CoV-2 test results available.

Primary outcomes include (1) SARS-CoV-2 symptomatic infection, confirmed by rRT-PCR or antigen test in respiratory samples from the nasopharynx or oropharynx and (2) moderate–severe COVID-19 disease, defined by hospitalization for over 24h, intensive-care unit (ICU) admission or death.

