Baseline demographic and health data are going to be collected, namely age, gender, municipality of residence, date of vaccination and type of vaccine used, number of doses, previous SARS-CoV-2 infection, and being in a clinically extremely vulnerable group due to immunodepression or respiratory disease [34]. These variables are going to be studied as potential confounders, as they may influence both the receipt of the vaccine and the occurrence of COVID-19.

The results will be compared in two periods: 1 June to 31 September 2021, corresponding to the fourth pandemic wave in Portugal and 1 November 2021 until the 2 March 2022 (fifth pandemic wave). Vaccine’s roll-out was fast in Portugal, being 50% of people fully vaccinated by 20 July 2021. Moreover, on the 22 September 2021, Portugal was the first country in the world hitting the milestone of 85% of the population fully vaccinated [35]. Initially, COVID-19 vaccines were only approved for people older than 16 (Comirnaty) or 18 years old (the other vaccines approved in the UE/EEA). In Portugal, vaccination of adolescents between 12 and 15 years old begun in August and for children from 5 to 11 years old was only approved in December of 2021. Therefore, children and adolescents under 18 years will be excluded from this study.

Data analysis will be performed using R Statistical Package^®^, Vienna, Austria (SPSS), 4.1.0 version. We will perform a descriptive analysis of all variables obtained within the scope of this research project. For continuous variables with a symmetric distribution, the mean and standard deviation are going to be used; if the distribution is not symmetric, the median and interquartile range will be chosen. Categorical variables will be described as absolute and relative frequencies.

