## 4. Discussion

This project aims to evaluate the effectiveness of vaccination against COVID-19, to produce scientific evidence that can support strategies for the prevention and control of pandemics. This might contribute to the planning of more suitable vaccination campaigns and to tackle phenomena such as vaccine hesitancy [37].

This will be the first study to evaluate the real-world effectiveness of the vaccination campaign against COVID-19 in people over 18 years old in Portugal. The study design described has important advantages, namely: (1) the cases and controls are selected in the same health care unit and, therefore, probably residing in the same geographic area and in the same sociocultural environment, reducing bias due to risk variation according to the location [2]; (2) cases and controls all sought care for COVID-like illness, which reduces the likelihood of bias related to seeking health care or testing, which is an advantage compared to traditional case control and cohort studies [2,27,29]; (3) the vaccination status is usually recorded before performing the test, prior to the knowledge of the result, so that a potential bias of differential misclassification of exposure is avoided [2].

As with other observational studies, this study may have limitations in internal validity that we will try to control in the study design and data analysis.

Vaccinated individuals may have more risk behaviours because they believe they are protected, resulting in underestimation of the vaccine effectiveness [2]. Furthermore, it will not be possible to directly measure vaccine effectiveness against specific variants due to the low proportion of genotyped cases. However, periods in which different variants were dominant will be analysed so that an approximation of vaccine effectiveness against these variants can be achieved, indirectly.

Confounding may occur when the vaccination status is associated with a person’s risk of being exposed to SARS-CoV-2. If, for example, people who choose not to be vaccinated are also those who do not adhere to individual protection measures, this can lead to an overestimation of vaccine effectiveness.

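### The second comparison period is labelled Omicron-dominant but starts 49 days before the protocol's own date for Omicron dominance, so its VE mixes Delta and Omicron

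*Protocol article*

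**What the plan says.** All references are to the protocol article.

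- **Aim.** The Abstract sets out to evaluate VE against symptomatic and severe disease before and after Omicron.
- **First period (1. Introduction).** "the fourth pandemic wave (1 June to 30 September 2021), dominated by Alpha and Delta variants". Of Delta, the section says that "by the week of 21 to 27 June 2021, the Delta variant became dominant".
- **Second period (1. Introduction).** "the fifth pandemic wave (1 November 2021 to 2 March 2022), Omicron-dominant".
- **Second period (2. Materials and Methods).** The results are to be compared between the two periods, the second being "1 November 2021 until the 2 March 2022 (fifth pandemic wave".
- **Date of Omicron dominance (1. Introduction).** The fifth wave "was dominated by the Omicron variant since the week of 20 to 26 December 2021".
- **First detection of Omicron (1. Introduction).** "The B.1.1.529 (Omicron) variant was first found in South Africa in November 2021".
- **Use of the periods (4. Discussion).** VE against specific variants cannot be measured directly because few cases are genotyped. Instead, "periods in which different variants were dominant will be analysed so that an approximation of vaccine effectiveness against these variants can be achieved, indirectly".

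**The concern.** The label and the dates disagree. The second period is offered as one in which Omicron was dominant, but it opens seven weeks before the date the protocol gives for that dominance. Methods uses the same dates for the planned comparison, so this is the analysis split and not loose wording in the background text.

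Calendar period is what represents variant in the pre/post-Omicron comparison. Patients seen from 1 November to 19 December are counted on the Omicron side. On the protocol's dates, the last dominant variant named for those weeks is Delta, which also dominated most of the first period. Part of the contrast is therefore Delta against Delta. If VE differs by variant, which is the premise of the comparison, the second-period VE is pulled towards the Delta value and the contrast is understated. The Conclusions intend the results to inform booster doses and variant-specific vaccine formulations.

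**Working it through.** The article gives no figure of its own for this point, so there is none to reproduce. The dates come from 1. Introduction and 2. Materials and Methods.

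**Calendar days, both end dates included**

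- Second period, 1 November 2021 to 2 March 2022: 30 + 31 + 31 + 28 + 2 = 122 days.
- Before the dominance week, 1 November to 19 December: 30 + 19 = 49 days, exactly 7 weeks.
- Share before dominance: 49/122 = 40.2%. Counted to the end of the dominance week (26 December): 56/122 = 45.9%.
- Remaining from 20 December to 2 March: 122 − 49 = 73 days.

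**Dominant variant in those 49 days.** The Introduction dates Delta dominance in Portugal to the week of 21 to 27 June 2021, and in another sentence to August 2021. Both precede November. It names no other dominant variant until Omicron in the week of 20 to 26 December.

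**Illustration of the dilution.** The assumptions, none of which the documents establish for this purpose, are:

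- VE of 70% for Delta (OR 0.30) and 40% for Omicron (OR 0.60). These are the ends of the range that 3. Results expects for symptomatic infection, assigned to variants by assumption.
- Coverage of 85% in controls throughout the period. Methods gives 85% as national full vaccination on 22 September 2021; its use for the study's controls is an assumption.
- A share s of second-period cases arising before 20 December, from 0.10 to 0.40. The documents give no weekly counts.
- One uniform VE per variant, and no cut or adjustment for calendar time within the period.

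Control odds of vaccination: 0.85/0.15 = 5.667.

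Vaccinated share of Delta cases: odds 0.30 × 5.667 = 1.70, share 1.70/2.70 = 0.630.

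Vaccinated share of Omicron cases: odds 0.60 × 5.667 = 3.40, share 3.40/4.40 = 0.773.

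Mixed share: p = s × 0.630 + (1 − s) × 0.773. Period OR = [p/(1 − p)]/5.667, and VE = 1 − OR.

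| s | p | Period OR | VE read as Omicron | Gap to 70% |
|---|---|---|---|---|
| 0 | 0.773 | 0.600 | 40% | 30 points |
| 0.10 | 0.758 | 0.554 | 44.6% | 25.4 points |
| 0.20 | 0.744 | 0.513 | 48.7% | 21.3 points |
| 0.40 | 0.715 | 0.444 | 55.6% | 14.4 points |

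**Dependence on the coverage assumption.**

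- As coverage tends to 0, the mixed OR tends to s × 0.30 + (1 − s) × 0.60. This gives 0.57 at s = 0.10 and 0.48 at s = 0.40, so VE of 43% and 52%.
- As coverage tends to 1, it tends to 1/[s/0.30 + (1 − s)/0.60]. This gives 0.545 and 0.429, so VE of 45% and 57%.

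The share s and the assumed gap between variants matter far more than coverage.

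**The case against.** The strongest defence has four parts.

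1. **The article is open about it.** It prints the dominance date close to the label, compares wave with wave over two windows of equal length (122 days each), and calls the variant estimate indirect and approximate. But the Discussion gives sparse genotyping as the reason for the approximation, and still describes the periods as ones in which the variants were dominant. The seven-week mismatch is not acknowledged.
2. **Methods plans to stratify by date of illness onset and to check interaction across strata.** This could expose the problem. As written, no cut is set at the switch to Omicron and the comparison period is not redefined, so it does not cure it.
3. **Little is lost if it is left.** The study is retrospective and dates are needed anyway, so a re-cut remains possible, and VE not split by period is untouched. This stands, and it limits how serious the point is. A cut fixed before results are seen is still better than one chosen afterwards.
4. **Other forces act on VE within the period.** 3. Results expects waning, and boosters may also matter, so Delta VE in November and December need not equal that of June to September. This stands, and it makes the net size of the bias uncertain.

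A reader might also infer three stronger things that the documents do not support:

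- **That 40% of second-period patients are pre-Omicron.** The figure is calendar time. With the peak on 25 January 2022 the patient share is probably smaller.
- **That the weeks before 20 December were free of Omicron.** The protocol dates dominance, not arrival in Portugal, and reports detection in South Africa in November followed by rapid spread.
- **That October patients are collected and then wasted.** Methods says patients "from 1 June 2021 until 2 March 2022, will be enrolled", and October lies in neither window. But 3. Results reports data obtained for both periods, so the enrolment dates may simply be the outer limits. No loss is shown.

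**Conclusion.** The concern holds as a mismatch between a label and the protocol's own dates, carried into the planned comparison: 49 of 122 calendar days (40.2%) of the period called Omicron-dominant precede Omicron dominance. The second-period VE therefore mixes Delta and Omicron. If VE differs by variant, the pre/post-Omicron contrast is diluted.

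The size is unknown, because the documents give neither patient counts by week nor VE by variant. Under the stated assumptions, the Omicron VE would read about 45-56% instead of 40%, and a 30-point gap would shrink to about 25-14 points. These figures show that the effect could be material; they are not estimates for this study.

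**What to change.** 1. For the Omicron estimate, start the period at the protocol's own dominance date: 20 December 2021 to 2 March 2022 (73 days). Assign patients by onset date or test date, and state which.
2. Keep 1 June to 30 September 2021 as the pre-Omicron comparator. Analyse 1 November to 19 December as a separate Delta/transition stratum. Pooling everything from 1 June to 19 December is less attractive: it would merge Alpha, Delta, a fast vaccine roll-out and waning into a single estimate.
3. Add a sensitivity analysis that drops the weeks around the switch.
4. Keep the wave-against-wave comparison as a descriptive secondary analysis, without the Omicron-dominant label.

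The cost is a change of wording and a recoded period variable within windows already being collected. 3. Results states that on 14 May 2022 data collection was ongoing and that analysis would follow its completion, so the cut could still be fixed beforehand. The downside is a smaller Omicron stratum and a somewhat wider interval for its VE.

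### The first study period blends Alpha-dominant and Delta-dominant weeks, so as the only stand-in for variant it gives no Alpha estimate and a slightly diluted Delta one

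*Protocol article*

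**What the plan says.** The Introduction of the protocol article defines two periods for comparison. The first is described as "the fourth pandemic wave (1 June to 30 September 2021), dominated by Alpha and Delta variants", and the second as "the fifth pandemic wave (1 November 2021 to 2 March 2022), Omicron-dominant". Within the first, the same section says: "In the beginning of the first period, the Alpha variant was dominant in Portugal, and by the week of 21 to 27 June 2021, the" (the sentence goes on to name Delta as dominant). An earlier paragraph of that section dates the change more loosely, with Delta "becoming dominant by August 2021 in Portugal". For the second period, the Introduction places Omicron dominance from the week of 20 to 26 December 2021.

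The Introduction also cites a Portuguese study of breakthrough infection as "suggesting lower effectiveness of the mRNA vaccines in preventing infection with the Delta variant", relative to Alpha.

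The Discussion (section 4) rules out direct measurement of VE by variant because few cases are genotyped. It then says that "periods in which different variants were dominant will be analysed so that an approximation of vaccine effectiveness against these variants can be achieved, indirectly". Section 2 (Materials and Methods) lists date of illness onset among the stratification variables but gives no cut-point. The only time contrast it defines is that between the two periods.

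**The concern.** When variants are not typed, the calendar boundary does the work of a variant label, so where it falls determines what each estimate describes. Three variants are mapped to two periods. The first period joins two variants for which the article itself cites evidence of different mRNA vaccine effectiveness, so its single odds ratio averages two quantities that the authors have reason to think unequal.

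No period isolates Alpha, and the value a reader would take as VE against Delta contains some Alpha cases. The two ways of dating Delta dominance add a smaller difficulty: anyone who wants to place a cut inside the period finds two sentences pointing to different dates.

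What is at stake is the indirect variant approximation in the Discussion. The abstract and Conclusions say that the study may inform variant-specific vaccine formulations.

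**Working it through.** **Inputs from the protocol article**
- Period 1: 1 June to 30 September 2021 (Introduction; section 2 prints the end as 31 September, read here as 30).
- Period 2: 1 November 2021 to 2 March 2022 (Introduction).
- Delta dominance: week of 21 to 27 June 2021, with a reference; elsewhere by August 2021 (Introduction).
- Omicron dominance: from the week of 20 to 26 December 2021 (Introduction).
- Expected VE against symptomatic infection: 40 to 70% (section 3).

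The article gives no weekly or variant-specific case counts and no figure for the blend, so there is no stated figure to reproduce.

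**Step 1. Day shares in period 1**
- Length: 30 + 31 + 31 + 30 = 122 days.
- Before the June week (1 to 20 June): 20 days, 20/122 = 16.4%.
- To the end of the June week (1 to 27 June): 27 days, 27/122 = 22.1%.
- Delta-dominant remainder: 102 or 95 days, 84% or 78%.
- If 1 August were used as the cut: 61 days, 50%.

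**Step 2. Day shares in period 2**
- Length: 30 + 31 + 31 + 28 + 2 = 122 days.
- Before 20 December: 30 + 19 = 49 days, 49/122 = 40%.
- To the end of that week: 56 days, 46%.
- From 27 December onward: 122 − 56 = 66 days.

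**Step 3. Size of the blend in period 1**

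Assumptions, none of them from the article: constant vaccine coverage of 70% in controls, VE of 70% for Delta and 80 or 90% for Alpha, and case share w equal to day share.

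The control odds of vaccination are o = 0.7/0.3 = 2.333. For each variant, the vaccinated proportion among cases is p = (1 − VE)·o / [1 + (1 − VE)·o]. The pooled proportion is p = w·p_Alpha + (1 − w)·p_Delta, and the pooled VE is 1 − [p/(1 − p)]/o.
- p_Delta = 0.700/1.700 = 0.412.
- p_Alpha = 0.233/1.233 = 0.189 at VE 90%, and 0.467/1.467 = 0.318 at VE 80%.

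| Alpha VE | w | pooled p | pooled VE | above Delta |
|---|---|---|---|---|
| 90% | 0.164 | 0.375 | 74.3% | 4.3 points |
| 90% | 0.221 | 0.363 | 75.6% | 5.6 points |
| 80% | 0.164 | 0.396 | 71.9% | 1.9 points |
| 80% | 0.221 | 0.391 | 72.5% | 2.5 points |

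Taking the share before the June week (16%), the shift is about 2 to 4 points. Counting the whole transition week as Alpha raises the upper end to just under 6.

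**Step 4. A wider assumed gap**

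Suppose the two ends of the article's expected range are assigned to the variants (70% Alpha, 40% Delta; this assignment is an assumption). Use the simpler mixture OR = w·0.3 + (1 − w)·0.6, with w now read as the Alpha share of unvaccinated cases. Pooled VE is then 1 − 0.551 = 45% at w = 0.164 and 1 − 0.534 = 47% at w = 0.221, which is 5 to 7 points above the Delta value. The shift therefore depends mainly on how far apart the two variants are assumed to be.

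**Step 5. Direction of the period contrast**

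If VE was higher against Alpha than Delta, Alpha days raise the period 1 estimate and enlarge the apparent fall to Omicron. If VE was higher against the variant circulating before Omicron, the 49 early days of period 2 raise that estimate and shrink the apparent fall. The two act in opposite directions, and the article gives no case counts with which to weigh them.

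**The case against.** The strongest reply is that the plan does not need an Alpha/Delta split. The abstract states the aim as a comparison of pre- and post-Omicron phases, and a pooled pre-Omicron stratum fits that. The mixture is disclosed in the definition of the period. The Discussion disclaims direct variant-specific measurement before offering an approximation. On the referenced June date, 78 to 84% of period 1 days are Delta-dominant. Stratification by onset date is planned, and a full protocol or analysis plan may hold the cut-points.

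Most of this stands, and it rules out several stronger readings:
- **That the article promises variant-specific VE and cannot deliver it.** It offers only an indirect approximation, and a mostly-Delta estimate is a rough one for Delta.
- **That the two Delta dates contradict each other.** A June date satisfies dominance by August. The wording is loose and needs aligning, and the pooling limits the estimate whichever date is used.
- **That the distortion reaches 12 points.** With 90% and 70% that needs half of period 1 cases to be Alpha (pooled VE about 82%), which means counting all of June and July as Alpha against the referenced June week.
- **That the fall to Omicron is overstated.** The early days of period 2 could offset it.

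The size is also soft. Day share is not case share. Coverage was not constant: section 2 gives 50% of people fully vaccinated by 20 July and 85% by 22 September. The assumed Alpha values lie above the article's expected 40 to 70% for symptomatic infection.

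What the reply does not remove is that the Discussion rests its approximation on periods of dominance. The article itself draws those periods, and none of them isolates Alpha or separates it from Delta. An onset-date stratum without a cut-point does not settle this.

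**Conclusion.** The point holds in a limited form. As drawn, period 1 yields one mostly-Delta blend: no value for Alpha, and a Delta value probably shifted by a few points. The estimate is about 2 to 4 points with assumed VE of 80 to 90% for Alpha and 70% for Delta at a 16% Alpha share, somewhat more at 22% or with a wider gap between the variants. It rests on assumed VE values, constant 70% coverage in controls, and case share equal to day share.

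The pooled pre/post-Omicron comparison remains legitimate for the stated aim. The net effect of variant mixing on it is undetermined, since 40% of period 2 days precede the week of Omicron dominance. For the same reason, a cut in period 1 alone would not give a clean Delta-versus-Omicron contrast.

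**What to change.** 1. In the Introduction, align the statement that Delta was dominant by August 2021 with the referenced week of 21 to 27 June 2021.
2. Keep the pooled pre/post-Omicron contrast as planned, and state that period 1 is an Alpha/Delta mixture and that period 2 begins before Omicron dominance.
3. Add a pre-specified variant-phase analysis. In period 1, take the Delta phase from 28 June (95 days) and report the Alpha phase (1 to 20 June) and the transition week descriptively. In period 2, make a matching cut at the week of 20 to 26 December 2021; with that week set apart, the Omicron phase runs from 27 December (66 days).
4. Rest the Discussion's indirect approximation on these phases, and limit it to Delta versus Omicron.

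The cost is small. Onset and test dates are already needed for the planned stratification and for time since vaccination, so this is re-coding and a change of wording. Section 3 reports that data collection was still under way and that the preliminary analysis would follow it, so the cuts could still be fixed in advance. The downside is fewer patients, and so somewhat wider intervals, in the phase-specific estimates. The pooled contrast loses no one.
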